### 2.6. Sample Size and Power Calculation

The sample size was determined to detect an anticipated change in GM alpha diversity of 25% from baseline between control and treated groups. Based on a previously published trial conducted to test the efficacy of personalized nutrition intervention on alpha diversity [24,25], in the case of healthy adult subjects a sample size of at least 200 in each intervention level, totalling 400 individuals, will allow us to obtain a statistical power of 80% (beta) and alpha = 0.05. In case of loss to follow-up, extra volunteers will be enrolled to compensate. Due to the lack of specific data for children, the above calculations were extrapolated to the children’s group.

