Level 1 (entry-level) intervention will consist in the use of i-Diet Stance4Health and the analysis of GM and metabolites. Level 2 (advanced level) will consist of the use of i-Diet Stance4Health and the analysis of GM and metabolites (as in the entry level), plus the use of a wearable wrist band only in adults, a metabolomics test to check the presence of metabolism disorders [18,19], and the intake of tannins extracts in pills for adults and in biscuits for children (treated group) or placebo (control group). The wearable band will be used to record physical activity, heart rate, blood pressure, and body composition as well as to refine food intake. Tannin extracts will be produced and distributed looking for a deeper modulation of the GM [16]. All data recorded in i-Diet Stance4Health and by the wearable band and results of the analyses will be recorded in specific databases. In detail, 200 Spanish and German adults will follow the entry-level intervention, and 200 will follow the advanced level intervention, equally divided into control and treated groups. The same criteria will be used for 400 Greek children (100 normal weight, 100 with obesity, 100 with gluten-related disorders, and 100 with allergy/intolerance to cow’s milk). Among them, half will be included in Level 1 and half in the Level 2 intervention.

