### 2.18. Statistical Analysis

The primary outcome (alpha diversity) will be analysed within each group using paired comparison t-tests to evaluate whether the changes from baseline to 12 weeks will be statistically significant. The absolute change (value at baseline subtracted from value after intervention for each subject) will be estimated with independent t sample tests. ANOVA will be used to analyse taxonomic diversity data and to assess the association of the GM composition with the phenotypic characteristics of the study population. Sensitivity analyses will be undertaken based on the assumption that missing outcomes are the worst possible, or the best possible, in different randomization groups. A significance value *p* < 0.05 will be considered statistically significant. Alpha diversity calculations and statistical analyses will be performed using various packages in the R platform, including the Vegan library (v2.5-2; Oksanen et al., 2012).

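### The target is a percentage change from baseline, but the groups are compared by an unadjusted t-test on absolute change; a baseline-adjusted comparison reported as a percentage would match the target and gain power at no cost in participants

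*Protocol article*

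**What the plan says.** Section 2.6 sets the target as "an anticipated change in GM alpha diversity of 25% from baseline between control and treated groups". It gives "a sample size of at least 200 in each intervention level, totalling 400 individuals" for the adults, with "a statistical power of 80% (beta) and alpha = 0.05". The basis is described only by reference: "Based on a previously published trial conducted to test the efficacy of personalized nutrition intervention on alpha diversity". The same calculation is carried over to the children.

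Section 2.3 says that each level is "equally divided into control and treated groups", which makes 100 per arm within each adult level.

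Section 2.18 fixes the analysis of the primary outcome. First, "The primary outcome (alpha diversity) will be analysed within each group using paired comparison t-tests". Then comes the comparison between groups: "The absolute change (value at baseline subtracted from value after intervention for each subject) will be estimated with independent t sample tests". The threshold is given as "A significance value *p* < 0.05 will be considered statistically significant", without saying whether the test is one- or two-sided. Stool is collected at T0, T1 and T2 (section 2.13), so every participant analysed for change has a T0 value.

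**The concern.** The target and the planned comparison are stated on different scales. Section 2.6 speaks of a percentage of baseline; section 2.18 tests a raw difference in index units. The article names no diversity index and no baseline mean, so a reader cannot convert one into the other. When the trial reports, the estimate will not answer directly whether the 25% was reached.

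The change score is also not the best use of the T0 value. Subtracting the baseline in full is efficient only when T0 and T2 are very highly correlated. At lower correlations it carries the noise of the baseline into the outcome. Regressing T2 on T0 lets the data choose the weight, and in a randomised trial it estimates the same treatment effect with smaller variance. What is at stake is precision on the primary endpoint and a result that can be read against the target.

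**Working it through.** **Inputs.** From the article: 25% of baseline as the difference between groups (section 2.6), 80% power and alpha 0.05 (section 2.6), 200 per adult level (section 2.6) split equally into 100 and 100 (section 2.3), independent t-test on T2 minus T0 (section 2.18). Assumed: a two-sided test, a range for the SD of change, equal SDs at T0 and T2, and a range for their correlation r.

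**Step 1: can the plan's 80% be reproduced?** Not without an SD. Solving for it instead:

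SD of change = 0.25 / [(1.960 + 0.842) × √(2/100)] = 0.25 / 0.396 = 0.631

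That is about 63% of the baseline mean (62.8% with the t distribution, standardised effect 0.398). One-sided it would be 71%. This figure is derived from the stated sample size and power; the article does not state it.

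**Step 2: power for 25% with 100 per arm, by assumed SD of change.** Power = Φ(0.25 / (SD × √(2/100)) − 1.960), with SD as a fraction of the baseline mean.

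| SD of change | Power for 25% | Difference detectable with 80% power |
|---|---|---|
| 30% | >99.9% | 12% |
| 40% | 99.3% | 16% |
| 50% | 94.2% | 20% |
| 63% | 80.1% | 25% |
| 70% | 71.4% | 28% |
| 80% | 59.9% | 32% |

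An SD below 63% raises power above 80%; only a larger SD lowers it.

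**Step 3: does the difference of scale by itself change the power?** If 25% means 25% of the baseline mean μ, the absolute difference is 0.25μ, and μ cancels when the SD is also expressed in μ. For an SD of 0.63μ, power is 80.1% whether μ is 1, 3.5 or 200. A simulation with 100 per arm, SD of change 63% and baseline coefficient of variation 10 to 20% gave 79 to 80% for absolute and 77 to 79% for relative change.

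**Step 4: what adjustment for T0 gains.** With a common SD σ at both visits:

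- variance of the change score: 2σ²(1 − r)
- residual variance of T2 given T0: σ²(1 − r²)
- ratio: (1 − r²) / [2(1 − r)] = (1 + r)/2

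Starting where the change-score test has 80% power for 25%, the adjusted power is Φ(2.802 / √((1 + r)/2) − 1.960), and the difference detectable with 80% power is 25% × √((1 + r)/2).

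| Assumed r | (1 + r)/2 | Adjusted power for 25% | Detectable difference |
|---|---|---|---|
| 0.3 | 0.65 | 93.5% | 20.2% |
| 0.5 | 0.75 | 89.9% | 21.7% |
| 0.7 | 0.85 | 86.0% | 23.0% |

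Simulation of the same comparison gave 94%, 90% and 85%, in agreement.

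**The case against.** The strongest reply is that nothing here is wrong. Sizing on a percentage and testing a mean change is common shorthand, and Step 3 shows that the percentage converts directly to an absolute difference. An independent t-test on change is valid under randomisation. The index and the SD are details that an article commonly leaves to the full protocol. All of this stands, so the absence of the index or SD is not held against the article.

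A reader might go further and infer that the stated power does not belong to the planned test. The article does not support that. It states no SD, so nothing contradicts the 63%, and a sample described as a minimum is consistent with a smaller SD and higher power. It is true that the scale can matter more for strongly skewed data: in simulated lognormal scenarios with an SD of change near 62%, the absolute-change test had 75 to 76% power. Those scenarios are assumptions, however, and do not show that the stated power is wrong.

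A reader might also infer that 63% is impossible, because a normal distribution that wide would put some diversity values below zero. The share is 1.2%, 5.6% or 10.9% at correlations of 0, 0.5 or 0.7. It requires normal raw values and equal spread at both visits, neither of which the article states; a positive, skewed index can have a large SD with no negative values. The 63% also rests on reading 25% as the difference between groups. If it is the change in the treated group and controls change by 5 to 10%, the difference is 15 to 20% and the implied SD is about 38% (15/0.396) to 50% (20/0.396).

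The objection does not remove the choice of method. A valid test can still be less efficient than one that uses the same data, and its result can still be on a different scale from the target.

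**Conclusion.** The concern holds in a limited form. The target is a percentage change from baseline, and the planned comparison is an unadjusted t-test on absolute change. The 80% power is neither confirmed nor refuted by the article.

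Replacing the change-score test by a T0-adjusted comparison is a clear improvement. It cuts the variance by 35%, 25% or 15% at correlations of 0.3, 0.5 or 0.7, which takes 80% power to about 94%, 90% or 86%. These figures assume equal SDs at T0 and T2, a linear relation between them, 100 per arm with complete data, and a two-sided test. If the SD of change is well below 63%, power for 25% is already high and the gain appears mainly as a narrower confidence interval. The correlation itself is not in the article.

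**What to change.** In section 2.18, replace the independent t-test on absolute change by a between-group comparison of T2 alpha diversity adjusted for T0 (ANCOVA). Report the treated-control difference as a percentage with its confidence interval, so that it can be read against the 25%. If the chosen index is positive and skewed, do this on the log scale, where the treated/control ratio gives the percentage directly; otherwise divide the adjusted difference by the baseline mean. An index that can equal zero needs a rule for zeros before logs are taken.

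In section 2.6, say that the 25% is the difference between groups, if that is what is meant, and restate the percentage difference detectable with 100 per arm under the adjusted analysis, with the SD and correlation assumed.

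The cost is wording in the protocol and the analysis plan and one recalculation. No participants, visits or samples are added, since T0 stool is already collected.

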### 2.2. Eligibility Criteria

Five study populations will be included in the study:(1)Apparently healthy adult subjects (both sexes), aged 20–65 years, with a body mass index (BMI) between 20–28 kg/m^2^, stable weight, ability to use a smartphone, and Internet connection availability. Exclusion criteria are the diagnosis of chronic gastrointestinal (GI) disorders, coeliac disease, or chronic diseases such as diabetes or other metabolic diseases; present pregnancy or lactation (<6 weeks before study start), or intention to become pregnant in the next 12 weeks; recent inflammation and/or long-term use of an-ti-inflammatory drugs; medically prescribed diet or specific dietary regimens for any reasons (i.e., high-protein diet, vegetarianism, veganism, etc.); antibiotic treatment (<3 months before study start); intake of antioxidant, pre- or probiotic supplements (<1 month before study start); intense physical activity (>10 h/week); alcohol consumption >21 drinks/week for men and >14 drinks/week for women.(2)Normal weight children (of both sexes), aged 6–11 years, with a BMI >5th and <85th percentile for age, gender, and height. Exclusion criteria are the diagnosis of chronic GI disorders and any other chronic disease, elimination diet, intake of probiotics (<2 weeks before study start).(3)Children (of both sexes) with obesity, aged 6–11 years, with a BMI ≥95th percentile for age, gender, and height. Exclusion criteria are the diagnosis of chronic GI disorders and endocrinopathies, intake of probiotics (<2 weeks before study start).(4)Children (of both sexes) with gluten-related disorders, aged 6–11 years, diagnosed with coeliac disease or wheat allergy (sIgE), on elimination diet. The exclusion criteria are the absence of symptoms.(5)Children (of both sexes) with allergy/intolerance to cow’s milk, aged 6–11 years, with an IgE-mediated milk allergy on an elimination diet from infancy, lactose intolerance (symptoms plus breath hydrogen positive test), overgrown IgE-mediated milk allergy but current aversion for milk, or nondefinable phenotype (children who avoid milk but do not belong to any of the previous phenotypes). Exclusion criteria are the diagnosis of other GI comorbidities.

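### The adult power figure carried over to children can hold only for the four child populations pooled within a level; a single population has 25 per arm and, on the adult assumption, about 28% power

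*Protocol article*

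**What the plan says.** All references are to the protocol article.

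- **Target (section 2.6).** "The sample size was determined to detect an anticipated change in GM alpha diversity of 25% from baseline between control and treated groups". The basis is given as "Based on a previously published trial conducted to test the efficacy of personalized nutrition intervention on alpha diversity", with no SD or standardised effect.
- **Adult size (section 2.6).** The number is set as "in the case of healthy adult subjects a sample size of at least 200 in each intervention level, totalling 400 individuals".
- **Power and alpha (section 2.6).** The article says of that number that it "will allow us to obtain a statistical power of 80% (beta) and alpha = 0.05".
- **Children (section 2.6).** "Due to the lack of specific data for children, the above calculations were extrapolated"; the sentence ends by naming the children as one group, in the singular.
- **Adult allocation (section 2.3).** For the second level, "200 will follow the advanced level intervention, equally divided into control and treated groups"; the first level also has 200 adults.
- **Child allocation (section 2.3).** "The same criteria will be used for 400 Greek children (100 normal weight, 100 with obesity, 100 with gluten-related disorders"; the remaining 100 have cow's milk allergy or intolerance. Half of the children go to each level.
- **Populations (section 2.2).** "Five study populations will be included in the study". Four of the five are paediatric, each with its own eligibility rules.
- **Analysis (section 2.18).** The change in alpha diversity is compared by independent-sample t tests. ANOVA is mentioned for taxonomic data and for relating microbiota composition to phenotype, but the treatment comparison has no population term.

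**The concern.** The adult calculation concerns one defined population. The children form four, with different conditions and diets, and three of those conditions are named in the abstract and introduction as part of the trial's purpose. A reader who sees one power statement for children beside four listed populations cannot tell which comparison it covers.

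If it is taken to cover each population, a non-significant result in, say, the children with gluten-related disorders could be given weight that 25 versus 25 cannot carry. If it covers the pooled group, it rests on a common effect and on the adult SD, and section 2.6 itself concedes that child data are lacking.

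**Working it through.** **Inputs.** Power 80% and alpha 0.05 (section 2.6). 200 adults per level, equally divided, so 100 per arm (sections 2.6 and 2.3). 400 children in four populations of 100, half per level, on the same criteria as adults (section 2.3). Assumptions: the test is two-sided, and the level and arm splits apply within each child population.

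**Cell size in children.**
- One population, one level: 400 / 4 / 2 / 2 = 25 per arm.
- One population, both levels combined: 50 per arm.
- All four populations, one level: 4 × 25 = 100 per arm, as in adults.

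**The plan's own figure.** The 200 per level cannot be reproduced forward without an SD, so I take the stated 80% as true and solve for the standardised effect d:

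d = (1.960 + 0.842) × √(2/100) = 0.396 (0.398 by noncentral t).

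If d corresponds to the 25% target, the implied SD of change is 25 / 0.396 = 63 percentage points of baseline.

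**Power at that effect.** Power ≈ Φ(d × √(n/2) − 1.960).
- n = 25: 0.396 × √12.5 = 1.401; Φ(−0.559) = 28.8% (28.1% by t).
- n = 50: 50.8% (50.5% by t).
- n = 100: 80%, by construction.

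**Detectable effect with 80% power at n = 25.** 2.802 × √(2/25) = 0.792, exactly twice 0.396, or about a 50% change instead of 25%. The noncentral t gives 0.809, or 0.809 / 0.398 × 25% = 51%.

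**Sensitivity at 25 versus 25.**
- One-sided 0.05, 80% at 100 versus 100: d = 0.352, power about 34%.
- Two-sided, 80% at 200 versus 200: d = 0.280, power 16 to 17%.
- One-sided, 80% at 200 versus 200: about 22%.
- SD assumed freely for a 25-point difference (two-sided): 94% (SD 25), 60% (SD 40), 42% (SD 50), 31% (SD 60), 20% (SD 80), 14% (SD 100). The smallest SDs do not fit the stated design: SD 25 would need only 16 per arm for 80% power.

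**How far pooling depends on a common effect (illustration only).** Suppose the 100 normal-weight children show no effect and the other three populations show the full adult effect. The pooled effect is then 0.75 × 0.396 = 0.297. At 100 versus 100, Φ(0.297 × √50 − 1.960) = Φ(0.141), or about 56%.

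**The case against.** The strongest reply is that nothing in the article is numerically wrong. The extrapolation is made to one children's group, and 400 children give 100 versus 100 per level, as in adults. A reader might infer that 80% is promised for each child population and that the design delivers 28% instead. The documents do not support this: no section states power per population, and separate eligibility definitions do not make each population a separately powered confirmatory comparison. This part of the reply stands.

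The reply can add that a condensed article may leave strata and subgroup reporting to the analysis plan, that the adults are themselves mixed (two countries, ages 20 to 65, BMI 20 to 28), and that analysing change from baseline already removes population differences in starting level. These points also stand. Only differences in mean change between populations would add variance to an unstratified pooled test, and the article gives no figure for them. The absence of a population term is therefore not an error by itself.

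What the reply does not remove is that the power statement is made in this article, next to four defined populations, without saying that it can apply only when they are pooled.

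**Conclusion.** The point holds as one of scope, not as an arithmetic error. The extrapolated 80% can refer only to treated versus control in the four child populations pooled within a level, and only if the adult effect and SD carry over to children.

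For one population within one level, power is about 28%, and the detectable effect is about twice the adult target. The 25 per arm follows from section 2.3. The 28% is conditional: it is back-solved from the article's own 80% claim with two-sided 0.05 and 100 per arm. The alternative readings of sidedness and of the basis for the 80% give 16 to 34%. On none of the readings that accept the stated 80% does a single population come near 80%.

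**What to change.** - In section 2.6, state that the 80% for children refers to treated versus control pooled over the four populations within a level (100 versus 100), and that it assumes the adult effect and SD.
- In section 2.18, analyse that comparison with population as a stratum or factor instead of a plain t test. Population is known at enrolment.
- State that population-specific comparisons are not powered (about 28% per level on the adult assumption) and will be reported as estimates with confidence intervals.
- Give the SD and sidedness behind the calculation, so that these figures can be checked directly.

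The cost is a few sentences and one model term, with no extra participants. The downside is a less favourable power statement for the individual child populations. If the sponsor does want each population to be confirmatory within each level, the adult assumption would require 100 per arm: 100 × 2 arms × 2 levels × 4 populations = 1,600 children, four times the planned number.

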### 2.7. Recruitment and Randomization

Adult male and female participants for the personalised nutrition intervention will be recruited thanks to the collaboration with companies working in the field of nutrition and dietetics, from existing databases, and using the German and Spanish Stance4Health Facebook pages. Moreover, advertisements in local newspapers or TV programs will be used, and flyers, handouts, and posters will be distributed and affixed. In the case of an insufficient number of recruited subjects, additional participants will be recruited through the involvement of the mayors of the cities/villages in which the intervention will take place. Children will be recruited from the clinics of the University Hospitals of Ioannina, Patras, and “Attikon”, Greece.

The random allocation sequence necessary to assign individuals to each of the two levels of intervention, and further to the “control” and “treated” groups, will be provided and managed by an investigator who will not take part in the participants’ recruitment.

The randomisation list will be concealed to the investigational site. It will be stored under lock and key until database closure. After receipt of the closed database, the randomisation allocation sequence will be sent to the survey centres for statistical analysis.

### 2.8. Blinding

Blinding of participants will be possible thanks to the use of a placebo instead of tannin pills and biscuits enriched in tannins. Blinding of trial personnel is not possible because of differences between the intervention levels.

Trial personnel who will enroll participants, data collectors, outcome assessors, and data analysts will be blinded to treatment allocation, and an employee outside of the research team will manage data in the computer on separate datasheets.

### 2.9. Data Collection

Follow-up assessments and data collection will be undertaken by trial personnel at the University of Granada in Spain, at Technische Universität Berlin, Berlin, Germany, and at the University Hospitals of Ioannina, Patras, and “Attikon” Greece.

### 2.10. Compliance

To ensure good compliance, participants will be given detailed instructions and training to learn how to use the nutritional app i.Diet Stance4Health. Moreover, the nutrition app is designed to generate notifications to remind users to log all meals or update the necessary data and to provide nutritional or physical activity tips and alerts when they deviate from healthy parameters. Finally, to increase consumer empowerment, periodic feedback of the collected data will be sent to participants (i.e., after each week deviation in energy intake, cholesterol, iron, and other nutrients will be launched by the app).

